### Participant identification and recruitment

Due to CAPT clinical practice and availability, it is anticipated that recruitment will take place in line with school terms and half terms where possible, resulting in recruitment of up to five cohorts of participant dyads during the recruitment period. Recruitment will be initiated after referral to, or re-referral within, CAMHS. All referrals aged between 5 and 11 years with a potential CD will be screened. Once a potential primary carer-child dyad has been identified and CAPT capacity has been confirmed, the local CAMHS practitioner will introduce the trial to them. If the primary carer is interested in participating, the primary carer and child will be provided with TIGA-CUB Information Leaflets and consent will be gained for initial researcher contact. In addition, as part of the process evaluation for the trial, primary carers will receive a questionnaire gauging their understanding of the trial and asking about their views on the recruitment process, and will be asked if they would be willing to consent to a process evaluation researcher contacting them subsequently to collect more detailed feedback. Responses will be reviewed so that recruitment processes can be refined for a confirmatory trial.

Where consent is given for initial researcher contact, the primary carer will be contacted and a meeting scheduled either at the primary carer’s home or at another appropriate location to explain the trial in greater detail, establish full trial eligibility, obtain consent, and undertake the baseline assessment. The dyad will have been given at least 24 h to read and digest the Information Leaflets previously provided, and will have had the opportunity to discuss them with their family and/or other health care professionals (e.g. GP) if they so wish, before being asked whether they would be willing to take part in the trial.

All primary carers will be asked to complete the AUDIT-C and DAST-10, plus the SDQ. Formal consent will not be required prior to completion of these measures, as completion will constitute implied consent. Those who decline at this stage will be offered TaU for their child. Those who complete these measures but score outside of the thresholds specified in the inclusion criteria will not be eligible to take part, and will also be offered TaU.

Where dyads fulfil all the eligibility criteria, the primary carer will be invited to provide informed written consent. Given the age of the children involved in the trial (5–11 years old), their formal consent will not be obtained, and the primary carer will provide consent for their inclusion. However, as per the Health Research Authority (HRA) guidance for research involving children, children will still be involved in the decision-making process with the right to voice their views and to influence the resulting decision, and will be provided with information that matches their capacity. Should the child actively object to taking part in the trial, then they will not be included, and reasons for non-participation will be recorded, where provided.

### Randomisation

Following confirmation of eligibility and consent, and subsequent to the baseline assessment being performed, dyads will be randomised by the trial researcher via the Clinical Trials Research Unit’s) (CTRU’s) automated 24-h randomisation system. Dyads will be randomised (1:1 basis) to receive mPCP or TaU. A computer-generated minimisation algorithm incorporating a random element will be used, stratifying for (1) site and (2) gender of child. If a dyad is randomised to mPCP in a CAMHS clinic in which multiple CAPTs are available to deliver the intervention, dyads will also be randomly allocated to the CAPT who will deliver the child’s intervention, with an allocation ratio proportional to CAPT availability, to avoid selection bias. Where only one CAPT works in a CAMHS, the CAPT will automatically be selected as the delivering CAPT. The CTRU will inform the CAMHS, but not the researcher (to preserve blinding), of the outcome of randomisation. The CAMHS will contact the primary carer to explain the outcome of the randomisation and to make an appointment for initiation of treatment. Therefore, participants and CAPTs will, of necessity, be aware of treatment allocation.

### Interventions

#### Manualised Psychoanalytic Child Psychotherapy (mPCP)

Qualified CAPTs who are current members of the Association of Child Psychotherapists (ACP), working in CAMHS, and trained in the trial intervention will deliver mPCP (referring to both sessions for the child and work with the primary carer and any other of the child’s parents/carers wishing to attend), using the TIGA-CUB manual. The manual is sufficiently flexible to accommodate the range of situations likely to be encountered in the trial, and will be reviewed (and updated if necessary) at the end of the feasibility trial by the Trial Management Group (TMG) to ensure that it is appropriate for a confirmatory trial.

Children will attend mPCP sessions of approximately 50-min duration each, delivered over 12 weeks at approximately weekly intervals (excluding breaks of no more than 2 weeks at normal school holidays). This will equate to a total of up to 12 sessions. The primary carer will attend parent work sessions of similar number, duration, and spacing. It is planned that the child and primary carer, respectively, will be seen separately either by the same CAPT or by two different CAPTs. The reason for this decision will be recorded. Where the child and primary carer are seen by the same CAPT, the sessions will, of necessity, take place at different times, but will take place in the same week as far as is practically possible. If the child and primary carer are seen by two different CAPTs, the sessions will either take place at the same time, or will take place at different times within the same week, where possible. Where the child and primary carer are seen by two different CAPTs at different times, the primary carer sessions will commence prior to those of the child. Following PCP practice, the day, time, and location of all sessions will be kept consistent unless there are exceptional circumstances, and the intervention will usually commence no less than 3 weeks prior to an end-of-term or half-term break so as to facilitate the establishment of the therapeutic alliance. A holiday break will nevertheless be incorporated where possible, to give the child and primary carer a ‘practice run’ at a therapeutic ending.

As with TaU, it is anticipated that some participants will miss sessions because of dropout (intermittent or complete) or mutually agreed early termination of treatment. Conversely, some may go on to receive more sessions, where this is deemed clinically appropriate, although it is anticipated that this will be the exception rather than the rule. In line with usual CAMHS practice, each local CAMHS will identify a named case manager for the CAPT(s) to liaise with, to provide assurance with regard to clinical governance.

All eligible CAPTs working within a recruiting CAMHS will be trained and supervised to deliver mPCP in the trial. CAPTs will receive appropriate training in the use of the manual and adherence to it, delivered by the chief investigator, and other relevant members of the TMG if necessary. Small-group supervision of participating CAPTs will be conducted approximately fortnightly, in person except in exceptional circumstances, by supervisors experienced in working with children with CD and in the use of the manual who will themselves attend termly supervision, to facilitate adherence to the manual and quality of care. Supervising CAPTs will be trained by appropriate members of the TMG. These arrangements will ensure a fair test of mPCP by using qualified CAPTs receiving regular clinical supervision, which is accepted best practice in CAMHS and in the ACP.

#### Treatment as Usual (TaU)

TaU will comprise the usual care offered by local CAMHS to children aged 5–11 years with CD. This treatment is likely to be highly diverse and may involve group and/or individual child and/or primary carer and/or family based work, delivered by a range of practitioners from a variety of professional backgrounds and theoretical orientations. The duration of TaU in CAMHS will vary considerably, but our scoping study demonstrated that the average amount of time spent in CAMHS is likely to be at least 33 weeks ([name], [name]. Scoping study in regional CAMHS in the north of England on children aged 5-11 with conduct disorders, unpublished). The confirmatory trial will be pragmatic, involving several collaborating CAMHS, and so currently, it would not be possible to specify what TaU should be. We will, therefore, monitor what it is in this feasibility trial and how this varies across CAMHS. Our scoping study will be used to inform data collected, and the duration of time that families spend within CAMHS will be recorded. It is, nevertheless, expected that CAMHS clinicians will be working in line with best practice, as per the NICE guidelines for children with CD [1]. In addition, in line with current best practice, it is expected that practitioners delivering TaU will be in receipt of supervision, and this will also be monitored as part of the trial. CAPTs at sites will not provide mPCP, non-manualised PCP, or TaU to dyads allocated to TaU and will, therefore, have no contact with TaU participants.

#### Both groups

All child and primary carer participants will be seen within CAMHS. Clinicians in both arms of the trial will have access to local Child Psychiatrists if medication or hospitalisation needs to be considered for any of the children participating in the trial. Routine care provided outside CAMHS will be unaffected for both arms.

### Data collection

#### Participant data

Participant assessments will be undertaken at the following time points:Baseline (prior to randomisation)4 months post randomisation8 months post randomisation (for participants recruited in the first 4 months of the trial).

A window of up to 2 weeks prior to randomisation will be recommended for baseline data collection (ideally, baseline and randomisation will occur on the same day) and plus or minus 2 weeks from the target follow-up date for outcome data. The feasibility of these windows will be recorded (see Table 1).

**Table 1 Tab1:** Summary of assessments

Assessment (and involvement*)	Timeline (months post randomisation)			
	Screening	Baseline	4 months	8 months
Eligibility and consent				
• Eligibility (inclusion criteria assessed by clinician)	x	x		
• Consent (P)		x		
Background, demographics, interview data (C, P, R)				
• Personal details (e.g. contact details)		x		
• Current comorbid physical/mental health		x	x	x
• Psychotropic medications		x	x	x
• Family composition		x	x	x
• Difficulties since randomisation			x	x
Clinical data (P, R, CSO)				
• Therapy details (CSO)			x	
• Therapist supervision details (therapist/supervisor)			x	
• Psychotropic medications details (CSO)			x	
• Referrals to other services (CSO)			x	
• Re-referrals to, or referrals within, CAMHS (CSO)			x	
• Baseline therapist data		x		
• Serious adverse event reporting	Ongoing collection			
Questionnaires				
• AUDIT-C (P)	x			
• DAST-10 (P)	x			
• SDQ (P)	x		x	
• EQ-5D-Y (P, proxy-completion and C, where able)		x	x	x (just P)
• EQ-5D (P)		x	x	
• CBCL (P)		x	x	x
• CBCL-TRF (T)		x	x	
• GHQ-12 (P)		x	x	
• Parenting Stress Index (P)		x	x	
• Beck Depression Inventory (P)		x	x	
• Parental Reflective Functioning Questionnaire (P)		x	x	x
• Healthcare Resource Use (P)			x	
Process evaluation				
• Primary Carer Recruitment Feedback Questionnaire (P)	x			
• ‘End of trial’ survey (P)			x	
• Semi-structured interview (sample of P)			x	
• Child Psychotherapist Focus Groups (CAPT)			**	

**C* child, *P* primary carer, *R* researcher, *CSO* clinical studies officer (from case notes), *T* teacher, *CAPT* child psychotherapist; **the focus group with CAPTs will be conducted after the final sessions of CP have been delivered

*AUDIT-C* Alcohol-Use Disorders Identification Test, *CBCL* Child Behavior Checklist, *CBCL-TRF* Child Behavior Checklist-Teacher Report Form, *DAST-10* Drug Abuse Screening Test, *EQ-5D* EuroQol 5 Dimensions, *EQ-5D-Y* EuroQol 5 Dimensions Youth, *GHQ-12* General Health Questionnaire, *SDQ* Strengths and Difficulties Questionnaire

At baseline and 4 months post randomisation, the following questionnaires will be used:Child Behavior Checklist (CBCL and CBCL-TR) [55, 56] (parental rating of child’s problem behaviours and competencies, and teacher rating of academic achievement and behaviour in class, in addition to attendance and performance)General Health Questionnaire 12 (GHQ-12) [52] (parental mental health)Parenting Stress Index (PSI) [57] (primary carer rating of their own functioning, functioning of child, and level of stress in the primary carer-child relationship)Beck Depression Inventory (BDI) (v2.0) [58] (screening instrument for adult depressive symptoms)Parental Reflective Functioning Questionnaire (PRFQ) [59–61] (measure of reflective functioning)EuroQol 5 Dimensions (EQ-5D™) (3-level) [62] (parental health-related quality of life)EuroQol 5 Dimensions Youth (EQ-5D-Y™) (3-level) (to measure child’s health-related quality of life as reported by the child via face-to-face researcher administration when the child is able to report for themselves, or by the primary carer as a proxy-respondent where the child is unable or unwilling to do so)

Questionnaires will be completed during researcher visits to participants’ homes, or failing that, by telephone or by post if necessary. Additionally, at baseline and at 4-month follow-up, the researcher will collect data from the primary carer on:Current comorbid physical/mental healthCurrent psychotropic medications (methylphenidate, other specified)Current family composition (i.e. who the child lives with)

At 8 months post randomisation, participants providing data will be asked to complete specific measures (CBCL, PRFQ, EQ-5D-Y) over the telephone in the first instance, or via a face-to-face visit or by post if necessary, to maximise follow-up data completion. The child’s school teacher will be asked to complete the CBCL-TR by post at baseline and 4 months post randomisation only.

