### Health economics

This component is included to check the completeness and ability to obtain resource-use data from dyads about both NHS and private costs and quality of life. Wherever possible, unit costs for resources will be obtained from national sources such as the *British National Formulary* (BNF) [63] and the Personal Social Services Research Unit (PSSRU) Costs of Health and Social Care [64]. NHS and Social Service resource use will be identified through direct observation of the treatment provided within the feasibility trial and through the structured questionnaire for collection of data on all other service use. We will assess the level of completeness of EQ-5D-Y as reported by the child and by the primary carer and evaluate any discrepancies using Quality-adjusted Life Years (QALYs) as the outcome.

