Statistical outcomes: (1) variability of self-reported outcome measures at baseline, 4 months; (2) clustering effect (ICC – intracluster correlation coefficient) relating to CAPTs in the intervention arm; (3) difference in self-reported outcomes available at 4 months per treatment arm; and (4) 95% confidence intervals (CI) for differences in outcomes between arms.

Health economic outcomes: (1) variability of the self-reported and proxy-reported EQ-5D-Y at baseline and 4 months; (2) completeness of and ability to obtain resource use data from dyads about both NHS and private costs; (3) exploratory cost-effectiveness analysis; and (4) suitability of a decision analysis model and appropriate time horizon to assess cost-effectiveness in the confirmatory RCT.

Process evaluation outcomes: (1) understanding of the recruitment process (with ideas for improving recruitment); (2) views on the intervention/trial; (3) reasons for declining to take part, dropping out of treatment, or withdrawing from the trial; (4) understanding of the contextual factors affecting involvement in the trial; (5) understanding of the barriers to, and enablers for, implementation; and (6) understanding of possible mechanisms of change.

Qualitative: establishment of (1) processes for successful recruitment of CAPTs; (2) procedure for training of CAPTs; (3) method for agreeing CAPT competence; and (4) procedure for ongoing supervision of CAPTs.

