### Sample size

The trial is designed to determine the feasibility of a confirmatory trial, not to assess proof of concept or evaluate effectiveness. It is generally recommended for feasibility studies that the analysis data set comprises a minimum of 30 participants per arm [65–67]. However, based on a review of the academic literature [68–78], estimates of the standard deviation (SD) of CBCL total score are already available, indicating that it is reasonable to assume a common SD across arms. We therefore require a minimum of 30 evaluable dyads across the arms to confirm the SD. Loss to follow-up has ranged from 8 to 38%, so we need up to 50 dyads randomised to guarantee 30 evaluable dyads. Treatment attendance has ranged from 40 to 95%. Assuming that we can reduce loss to follow-up to 10% at 4 months, randomising 60 dyads on a 1:1 basis will allow us to estimate the pooled SD with a 95% CI with expected width of 0.39 multiplied by SD, loss to follow-up with a 95% CI with expected width ± 7%, and treatment attendance in the intervention arm with a 95% CI with expected width of between ± 8 to 18%. It is expected that 60 dyads will provide sufficient opportunity to establish robust recruitment and retention strategies for a confirmatory trial.

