### Health economic analysis

The health economist will be responsible for health economic analysis. We will evaluate the completeness of data and rate of missing data on individual questions to inform the methodology and the perspective to be used within the confirmatory trial. Although the cost-effectiveness analysis at this stage will only be exploratory, the incremental cost-effectiveness of a second-line mPCP intervention compared to TaU for children aged 5–11 years with treatment-resistant CD and their primary carers will be examined. We will also calculate indicative costs for the interventions.

Utility weights will be obtained from the EQ-5D-Y data as reported by the child or by the primary carer as a proxy-respondent for the child and collected as part of the feasibility trial follow-up. We will also consider aggregating utility gains, accumulating child and primary carer utility obtained from the EQ-5D. An exploratory cost-effectiveness analysis will be carried out on complete cases only (i.e. completion at all time points) and with imputations (multiple imputations based on age, gender, and treatment), and a set of within-feasibility trial sensitivity analyses will be undertaken.

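### The protocol gives two incompatible rules for who completes the EQ-5D-Y at baseline and 4 months, and only one of them supports the planned child–carer comparison.

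*Protocol article*

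**What the plan says.** Five places in the protocol article bear on who completes the EQ-5D-Y.

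- **Participant data, list of questionnaires (baseline and 4 months).** A child who can answer does so, with the researcher present. The entry then gives the alternative: "or by the primary carer as a proxy-respondent where the child is unable or unwilling to do so". Carer report is a fallback.
- **Table 1, in the same section.** The row reads "EQ-5D-Y (P, proxy-completion and C, where able" and is marked at baseline and 4 months. At 8 months it is restricted to the carer.
- **Health economics.** "We will assess the level of completeness of EQ-5D-Y as reported by the child and by the primary carer and evaluate any discrepancies", with QALYs as the outcome.
- **Outcomes, health economic outcomes.** The list includes "variability of the self-reported and proxy-reported EQ-5D-Y at baseline and 4 months".
- **Health economic analysis.** "Utility weights will be obtained from the EQ-5D-Y data as reported by the child or by the primary carer as a proxy-respondent". No rule says which report is used when both exist, or that a child keeps the same respondent over time.

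**The concern.** The questionnaire list says one report per child per visit. Table 1 says a carer report for every child and a child report as well where possible. These are different data collection instructions, and a researcher at the visit cannot follow both.

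The choice decides whether the planned child–carer comparison can be made within child. With one report per visit, the two kinds of report come from different children, sorted by ability and willingness to answer. A difference between them then says little about how the respondents differ. The same rule lets the respondent change between visits, so a child's change in utility can contain a change of respondent.

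This matters here because the Aims and objectives section asks how quality of life data should best be collected, and by which methods from carers and children. Child report against proxy report is part of that question. A later analysis plan can choose between reports that were collected. It cannot recover carer forms that were never filled in.

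**Working it through.** The protocol states no figure to reproduce on this point. The check compares the passages and then counts pairs under each rule.

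**1. Passages side by side**

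| Place | Rule or need | Fits one report per visit? | Fits carer for all plus child where able? |
|---|---|---|---|
| Participant data, questionnaire list | child, or carer if the child cannot or will not | yes | no |
| Table 1, baseline and 4 months | carer and, where able, child | no | yes |
| Health economics | completeness by both respondents, and their discrepancies | not within child | yes |
| Outcomes | variability of both versions at baseline and 4 months | only in different children | yes |
| Health economic analysis | utilities from child or carer | yes | yes, if a respondent is chosen |

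**2. What the fallback rule does to the comparison**

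Let C be the child-reported utility and P the carer-reported utility for the same child at the same visit. The quantity wanted is the mean of C − P among able children. With one report per visit the only available contrast is

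mean(C | able) − mean(P | not able) = mean(C − P | able) + [mean(P | able) − mean(P | not able)].

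Here 'not able' includes children who are unwilling. The bracket is the difference in carer-rated health between the two groups of children. It cannot be estimated, because P is never collected for able children.

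**3. What it does to change over time**

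For a child proxied at baseline who self-reports at 4 months,

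C(4) − P(0) = [P(4) − P(0)] + [C(4) − P(4)].

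The second bracket is the respondent effect. It cannot be separated out, because P(4) is missing.

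**4. Number of pairs**

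Inputs from Sample size: "randomising 60 dyads on a 1:1 basis", and "Assuming that we can reduce loss to follow-up to 10% at 4 months". Dyads with data are 60 at baseline and 60 × (1 − 0.10) = 54 at 4 months. The share of children able to self-report is not in the document, so a range is assumed. Pairs = dyads × share able.

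| Share able (assumed) | Fallback rule, either visit | Table 1, baseline | Table 1, 4 months |
|---|---|---|---|
| 25% | 0 | 15 | 13.5, about 14 |
| 50% | 0 | 30 | 27 |
| 75% | 0 | 45 | 40.5, about 41 |
| 100% | 0 | 60 | 54 |

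**5. Eight months**

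Table 1 has the carer only, for the early recruits who are followed that far. There are no pairs at that visit under Table 1. If Table 1 governs throughout, however, a carer series runs unbroken over baseline, 4 and 8 months, while a child self-report series stops at 4 months.

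**The case against.** The strongest reply is that the document, read as a whole, intends both reports. Table 1 is the assessment schedule, and the Health economics and Outcomes sections agree with it. The either/or wording that governs collection stands only in the description of the instrument. This part of the reply stands. A reader of that description might infer that the discrepancy analysis has no pairs and that QALYs mix respondents within a child. The documents do not support either as a fact about the plan, because Table 1 supplies pairs and a constant carer series.

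A reader might also infer that a respondent switch at 8 months is built in. It is not. It arises only if the fallback rule was used earlier, or if child report is chosen for the QALY and carried past 4 months. No 8-month QALY comparison is stated. The 8-month visit covers early recruits only and is there to test longer-term data collection.

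Three further replies stand in part.

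- Some of the feasibility question survives the fallback rule, since the share of children who self-report would still be seen. The within-child discrepancy would not.
- The Health economic analysis section does not say that child and carer reports are merged into one series. It does not exclude it either.
- The article is abridged, and a more detailed analysis plan is to follow. The choice of main respondent can be left to that plan and is a judgement. The contradiction cannot, because it lies in printed instructions on what to collect.

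**Conclusion.** The point holds as an internal contradiction about data collection. The questionnaire list under Participant data sets an either/or rule, and Health economic analysis repeats the 'or' for utilities. Table 1 schedules both reports, which the discrepancy analysis needs and the listed outcomes fit.

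The consequence is conditional on which instruction is followed. Under the fallback rule there are no within-child pairs at baseline or 4 months, and the respondent can change between visits. Under Table 1 there is one pair per child able to self-report, at most 60 at baseline and about 54 at 4 months. The 54 rests on the protocol's assumed 10% loss. The real counts depend on the share able to self-report, which is not given; if half were able (an assumption), they would be 30 and 27.

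The severity is modest, because the cost-effectiveness analysis is exploratory. No size can be put on any bias in the utility difference between arms, since the documents give no figure for the respondent effect or for how often children would switch.

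**What to change.** - **Participant data.** Reword the EQ-5D-Y entry to match Table 1: the carer completes the proxy version for every child at each scheduled visit, and the child self-reports in addition, where able, at baseline and 4 months. Record the respondent on every form.
- **Health economics.** State that the discrepancy is estimated within child, from the pairs, and report the number of pairs at each visit.
- **Health economic analysis.** State that each exploratory QALY uses one respondent type held constant within child, with the other type as a sensitivity analysis. Which type is the main one is a judgement. Only the carer series can reach 8 months under Table 1.

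The cost is one short extra form for carers who are already completing questionnaires. Relative to Table 1, nothing is added.
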